**DURATION**

June 2012-June 2013

**ABSTRACT**

**Background:** Diabetes mellitus is an important complication of pregnancy with adverse effects on both mother and fetus. Poor control of pre-gestational diabetes during the period of organogenesis increases the risk of major congenital malformations. While insulin is effective in controlling high blood glucose levels, otherwise resistant to diet and exercise management, several factors hinder its use. Metformin has been found to be a convenient, cheap, effective and safe hypoglycaemic agent in some countries and it is likely to do same among Ghanaian women.

**Aim:** The main aim of this study is to determine if metformin monotherapy or metformin in combination with insulin is equally effective at attaining and maintaining glycaemic targets compared to insulin monotherapy in the management of gestational diabetes mellitus and type 2 pre-gestational diabetes mellitus in Ghanaians.

**Methodology:**  A prospective randomized comparative study is proposed. Patient selection and randomization will be done using balloting with opaque envelopes. Participants will be followed through their index pregnancy with 2-weekly glycaemic profile monitoring and maternal weight gain. Babies delivered will be followed till the sixth week post-delivery measuring birth weight, incidence of birth trauma and neonatal intensive care unit (NICU) admission rates. Both laboratory and clinical data will be recorded and analyzed.

**Expected outcome:** It is expected that pregnant diabetics treated with metformin will have a lower 2HPG levels at the end of the study than those treated with insulin. The 2-hour post prandial glucose (2HPG) level is the measure selected to estimate the effectiveness of glycaemic control.

In addition NICU admissions are expected to be higher in the insulin group than metformin group.

**BACKGROUND**

Diabetes Mellitus is a metabolic disorder of multiple aetiology characterized by, chronic hyperglycaemia with disturbance of carbohydrate, fat and protein metabolism resulting from defects in insulin secretion, insulin action, or both ^1.^  Diabetes Mellitus is broadly grouped into Type I (Insulin Dependent Diabetes Mellitus) and Type II (Non- Insulin Dependent Diabetes Mellitus); the latter is the focus of this study. Diabetes Mellitus in pregnancy consists of pre-gestational Diabetes Mellitus and Gestational Diabetes Mellitus. Gestational Diabetes Mellitus is characterized by hyperglycaemia of varying severity, diagnosed during pregnancy (without previously known diabetes) and usually (but not always) resolving within six weeks of delivery^1^. The prevalence of diabetes mellitus world- wide is projected to increase.^2^

A study in Nigeria estimated the incidence of Diabetes Mellitus (DM) among pregnant women as 1.7%. Pre-gestational diabetes accounted for 39% while Gestational Diabetes was responsible for 61% of cases.^3^ There is no national data on the prevalence of DM among pregnant women in Ghana. Data from Greater Accra estimates the crude prevalence of Diabetes Mellitus as 6.3%^4^. It is estimated that 3-10 % of pregnancies are complicated by Diabetes Mellitus.^5, 6^

Diabetes mellitus is an important complication of pregnancy with adverse effects on both maternal and fetal outcomes. Treatment options of diabetes complicating pregnancy are limited. Several classes of medicines have been developed based on the pathophysiology of diabetes and are being used as monotherapy or combination therapies with varying efficacies in the general population of diabetics. In pregnant diabetics however, exercise and dietary management followed by insulin therapy where dietary management have failed is the general trend. Few countries have added some oral hypoglycaemic agents to this management, but lack of adequate data on efficacy and safety in the pregnant population has slowed this development in several countries.

The use of insulin has traditionally been the main stay in the management of DM in pregnancy not adequately controlled on diet and exercise. Though effective, the use of insulin is associated with some disadvantages such as the inconvenience of repeated injections, high cost, storage problems, hypoglycaemia, and fetal macrosomia amongst others. In one Indian study the cost of insulin was found to be ten-fold higher than metformin.^7^

A number of studies have examined the role of oral anti-diabetic medications in managing this condition in pregnancy. Metformin is one of the promising agents being widely used for this indication in many countries. It was first synthesized in the 1920s but was soon forgotten for the next two decades. Its history has been traced back to the use of a perennial herb, Galega officinalis in folklore medicine for the treatment of symptoms now known to be associated with DM.^11^

The first clinical trial of Metformin was performed by Sterne; He coined the name "Glucophage" (glucose eater) for the drug and published his results in 1957.^8^

Recent studies including randomized controlled studies suggest that metformin is more convenient, cheaper, effective and safe in pregnancy to mother and baby.^7, 9, 10^

**PROBLEM STATEMENT**

Diabetes Mellitus is a common disease in the adult population in both developed and developing countries. In developing countries in particular type 2 diabetes mellitus appears to be on the ascendancy because of life style changes and changing trends in dietary habits. As the disease burden increases in the general population it is expected that its prevalence in pregnancy will also increase. Pregnancies complicated by diabetes mellitus often require specialized care because of adverse maternal and fetal outcome if not properly managed. While several pharmacological options are available to diabetics in the general population for glycaemic control, the pregnant diabetic is often restricted to only insulin following dietary and exercise management failure. Insulin may not be affordable in low income countries. Frequent power outages or the absence of electricity also hinders its use in rural areas. In addition adherence to the frequent injections may be low.

Metformin taken orally is cheaper, more accessible and more user-friendly compared to insulin. Metformin is therefore a logical option for pregnant diabetics in Ghana. Recent clinical trials support metformin use in pregnancy, but lack of such data in Ghana still makes metformin use controversial. Its use during pregnancy has been hampered by lack of data on its efficacy and safety in pregnancy.

Another problem is that the pharmacogenetics of metformin does not support extrapolation of research findings from one place to another since its excretion is influenced significantly by a variant allele. Treatment failure or toxicity could occur in patients carrying the variant allele (*SLC22A2*).^16^

**HYPOTHESES**

- The glycaemic control will be equally effective with metformin therapy compared to insulin in pregnant diabetics in Ghana.
- Weight gain in mother and baby will be significantly lower on metformin therapy compared to insulin.

*Rationale:* Metformin has been shown to be equally effective and safe as insulin in the management of GDM. Poor compliance to insulin due to high cost, accessibility, storage difficulties and the discomfort of repeated injections is expected to make metformin a more suitable choice.

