**AIM**

The aim of this study is to determine if metformin monotherapy or metformin in combination with insulin is more effective at attaining and maintaining glycaemic targets compared to insulin monotherapy in the management of gestational diabetes mellitus and type 2 pre-gestational diabetes mellitus in Ghanaians.

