**Treatment failures**

Supplemental insulin for treatment failures in the Metformin group will be prescribed according to the same protocols in the insulin group.

DATA COLLECTION

Basic demographic data will be recorded. They will be followed through their index pregnancy, with 2-weekly blood glucose checks in hospital. All laboratory samples will be collected and analyzed at the diabetes research laboratory by staff of the same laboratory. Venous blood will be used for blood glucose profile analysis. Analysis of Fasting Blood Glucose (FBG), one- hour post-prandial glucose (1HPG), two- hour post-prandial glucose (2HPG) will be done using the Mindray BS-400^®^ (Mindray Medical Int. Ltd, China) chemistry analyzer. The method for glucose determination will be enzymatic photometric testing. Urinalysis, weight records (using Seca^®^(gmbh&Co. Kg Germany)) and cost of treatment will also be documented. The optimal dose of metformin required for optimal glycaemic control will be recorded for each patient. Peri-partum events like gestational age at delivery, type of delivery, fetal birth weight, and NICU admissions will be retrieved from patient notes.

STATISTICAL ANALYSIS

In analyzing the data, summary statistics will include appropriate tables and charts. Categorical data will be represented by pie and bar graphs and continuous data with histograms.

For inferential statistics, significant difference of mean observations using one-tail student’s t-test and z-score for differences in proportions where applicable. The differences in trends of glycaemic profile over time between the study groups will be assessed by two-way repeated measures analysis of variance (ANOVA).

Significance level (p-value) will be set at α = 0.05. Data analysis will be done using statistical package for social science **(SPSS** version 20).

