**EXPECTED OUTCOME**

It is expected that pregnant diabetics treated with metformin will have a lower 2HPG levels at the end of the study than those treated with insulin. The primary outcome is the difference in the 2HPG level between the metformin and insulin group. The rationale for selecting 2HPG is that by its mechanism of action, metformin is expected to have a more significant blood glucose lowering effect in the postprandial period than the fasting period. Hyperglycaemia in the prandial period is related to insufficient suppression of hepatic glucose output, poor insulin release and ineffective glucose disposal in target tissues (especially muscles) by insulin (insulin resistance) and metformin affect all these Biophases.^30-32^

Secondary outcomes to be measured include glycaemic profile (measured by FBG, 1HPG, and HB1AC), fetal birth weight, maternal weight gain and caesarean section rate which are expected to be lower in the metformin group, number of NICU admission which is expected to be higher in the insulin group. If found to be effective it may form the basis for developing a policy for Diabetes Mellitus care in pregnancy at primary and secondary level of healthcare instead of the current tertiary level of care.

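### The protocol states both equal and superior effectiveness as its objective, but is sized and tested only for a difference, so it cannot support an equal-effectiveness claim

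*Protocol*

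**What the plan says.** The protocol describes what it sets out to show in four places, and they differ.

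- Abstract, aim: whether metformin alone or "metformin in combination with insulin is equally effective at attaining and maintaining glycaemic targets compared to insulin monotherapy".
- Hypotheses, first item: "The glycaemic control will be equally effective with metformin therapy compared to insulin in pregnant diabetics in Ghana".
- Aim: nearly the same sentence as the abstract's, but now "metformin in combination with insulin is more effective at attaining and maintaining glycaemic targets compared to insulin monotherapy".
- Expected Outcome, also in the abstract: "It is expected that pregnant diabetics treated with metformin will have a lower 2HPG levels at the end of the study", compared with insulin.

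The endpoint is clear: "The primary outcome is the difference in the 2HPG level between the metformin and insulin group". The Sample Size Determination section bases 47 per group on the difference in 2HPG expected at 34 weeks. It takes 4 mg/dl (0.22 mmol/L) as the minimum difference, with 80% power and α = 0.05, and gives neither an SD nor the number of sides. The Statistical Analysis section plans "significant difference of mean observations using one-tail" Student's t-tests, a z-test for proportions and a two-way repeated measures ANOVA, all at 0.05. The direction of the tail is not stated. No section gives an equivalence or non-inferiority margin, or a rule based on a confidence interval.

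**The concern.** Equal effectiveness and greater effectiveness are different questions with different null hypotheses. A superiority test starts from no difference and looks for evidence against it. An equivalence or non-inferiority test starts from a difference at least as large as a margin and looks for evidence against that. The protocol states both objectives but provides the tools for only one. Under the planned analysis, the first hypothesis could appear confirmed only through a failure to reach significance, and that does not show equality.

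The Expected Outcome section says that, if metformin is found effective, the result may inform policy on moving diabetes care in pregnancy to primary and secondary level. The reader of such a result needs to know which claim the trial was built to test.

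**Working it through.** **1. What kind of calculation gives 47.** No SD is given, so 47 cannot be reproduced independently. It can be solved backwards from n = 2 × [SD × (z_α + z_0.80) / Δ]², with Δ = 4 mg/dl and n = 47:

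- one-sided 0.05: SD = 4 × √(47/2) / (1.645 + 0.842) = 7.80 mg/dl (about 0.43 mmol/L)
- two-sided 0.05: SD = 4 × √(47/2) / (1.960 + 0.842) = 6.92 mg/dl (about 0.38 mmol/L)

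A noncentral-t version gives 7.74 and 6.85 mg/dl. The 52 recruited per group is 47 × 1.10 = 51.7, rounded up. The calculation is therefore of the superiority type: 4 mg/dl enters as a difference to detect, not as a margin to exclude.

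**2. What a non-significant result would mean.** If the drugs are truly equal, a one-tailed test at 0.05 is non-significant with probability 1 − 0.05 = 0.95, whatever the sample size or SD. If the true effect lies opposite to the tested tail, the probability exceeds 0.95. Non-significance therefore does not separate equal from worse.

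**3. What 47 per group could support as non-inferiority.** The standard error is SD × √(2/47) = 0.2063 × SD. With one-sided 0.025, 80% power and no true difference, the supportable margin is (1.960 + 0.842) × SE = 0.578 × SD. The 95% confidence interval half-width uses t = 1.986 on 92 degrees of freedom for the assumed SDs, and z = 1.960 for the SDs implied by n = 47.

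| SD (mmol/L) | Source | 95% CI half-width | Supportable margin |
| --- | --- | --- | --- |
| 0.38 to 0.43 | implied by n = 47 | 0.16 to 0.18 | 0.22 to 0.25 |
| 1.0 | assumed | 0.41 | 0.58 |
| 1.5 | assumed | 0.61 | 0.87 |
| 2.0 | assumed | 0.82 | 1.16 |

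Conversely, at the implied SDs of 6.92 to 7.80 mg/dl, the number per group is 47 to 60 for a margin of 4 mg/dl and 188 to 239 for 2 mg/dl.

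**4. Power cost of a two-sided 95% interval.** If 47 was derived one-sided (SD 7.80 mg/dl), SE = 7.80 × √(2/47) = 1.61 mg/dl and 4/1.61 = 2.486. Power is Φ(2.486 − 1.645) = 0.80 one-sided at 0.05, and Φ(2.486 − 1.960) = 0.70 two-sided at 0.05.

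**The case against.** The strongest defence is that the Aim, Sample Size Determination, Statistical Analysis and Expected Outcome sections can be read together as a superiority trial on 2HPG, with the equal-effectiveness wording left over in the abstract and the hypothesis. A significant result favouring metformin would then support the Aim as written. That stands. A reader might infer that the trial can support no main conclusion at all, but the documents do not bear that out.

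Four other strong readings also go too far.

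- **That the t-test is the only test.** A z-test and a repeated measures ANOVA are also planned. The ANOVA F test has no direction and could flag worse control on metformin, although it cannot show equivalence.
- **That the tail is stated to point towards metformin.** The protocol says only that the test is one-tailed, and the sample-size text names no direction. The direction is inferred from the Expected Outcome section.
- **That a null result will be reported as equality and become policy.** No section says so, and the policy remark is conditional on metformin being found effective.
- **That a noisier trial makes a false finding of equality more certain when metformin is worse.** With metformin 0.5 mmol/L worse and the tail towards metformin, the chance of non-significance falls from 0.99998 to 0.998 as the assumed SD rises from 1.0 to 2.0 mmol/L. Values near 1 are largely a property of any one-tailed test and do not measure a defect of this trial.

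It could also be said that a separate analysis plan may supply a margin. That would not make the abstract, Hypotheses and Aim sections agree, and the sample size is already fixed in the protocol from a difference.

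**Conclusion.** The point holds in a limited form. The stated objectives are incompatible, and nothing in the protocol resolves them. The sample size and all planned tests address a difference. The design can support superiority but gives no basis for claiming equal effectiveness.

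The conflict in wording and the 95% non-significance rate under true equality need no assumption about the SD. The supportable margins do. They run from 0.22 to 0.25 mmol/L at the SDs implied by n = 47, up to 1.16 mmol/L at an assumed SD of 2.0 mmol/L. Whether 47 per group suffices for non-inferiority cannot be settled without a margin and an SD. The fall in power to about 70% applies only if 47 was derived one-sided.

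**What to change.** Choose one primary hypothesis and use it in the abstract, Hypotheses, Aim, Sample Size Determination, Statistical Analysis and Expected Outcome sections.

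**Superiority (the cheapest route).** This matches the Aim, the basis of the sample size and the expected outcome. Reword the first hypothesis and the abstract's aim. Report the two-sided 95% confidence interval for metformin minus insulin in 2HPG at 34 weeks, with a test consistent with that interval. State that a non-significant result is inconclusive and will not be described as equal effectiveness.

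**Equal effectiveness, if kept.** State and justify a non-inferiority margin for 2HPG before analysis. Make the claim only if the upper limit of the two-sided 95% confidence interval for metformin minus insulin lies below the margin. State the SD and what 47 per group delivers against that margin. Reconcile this with the Metformin Group section, which removes women given supplemental insulin from the metformin group and counts them as treatment failures, although both versions of the aim include metformin combined with insulin. Removing them could flatter metformin in a non-inferiority comparison.

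**Cost.** The superiority route needs rewording and an interval from the same data, at the price of a weaker claim after a null result and the possible loss of power from 80% to about 70%. The non-inferiority route needs more than wording, because the sample size must be checked against the margin. The sample-size text describes recruitment in the past tense, so adding participants may no longer be possible.

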**AIM**

The aim of this study is to determine if metformin monotherapy or metformin in combination with insulin is more effective at attaining and maintaining glycaemic targets compared to insulin monotherapy in the management of gestational diabetes mellitus and type 2 pre-gestational diabetes mellitus in Ghanaians.

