**Metformin Group**

In the Metformin group, starting dose of Metformin will be 500mg once a day and increased gradually over two (2) weeks, to meet glycaemic targets of FBS < 5.1 mmol/L, 1HPG < 10.0mmol/L and 2HPG < 8.5 mmol/L.

The maximum dose will be 2500mg per day. Insulin will be added if targets cannot be reached on metformin alone at maximum doses. Subjects that receive supplemental insulin will be excluded from the metformin group and analyzed for the purpose of this study as treatment failures. The quantity of supplemental insulin will be documented for analysis.

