**Insulin group**

In the Insulin group both soluble insulin and premixed insulin will be prescribed. There will be no brand restriction. Both premixed insulin and soluble insulin will be administered subcutaneously in the deltoid region. Total daily dose of premixed insulin at initiation will be calculated for most patients as 0.3 IU/kg body weight. However for patients admitted with high blood glucose levels they will be managed on sliding scale with soluble insulin their starting dose will be based on total daily requirement. The total daily dose will then be divided into two: two-thirds of the dose will be administered in the morning 30 minutes before breakfast and one-third of the daily dose will be administered in the evening 30 minutes before supper. The total dose of insulin will be titrated for each patient to achieve the above glycemic targets. Patients who may not achieve glycemic targets on their out-patient doses after attempts at titrations will be admitted to the ward and treated with soluble insulin to determine their new optimum insulin requirements. All patients will be educated by both nurses and doctors while on admission on the disease and self-administration of the correct doses of insulin before discharge.

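### The aim concerns reaching and keeping glucose targets, but no listed outcome compares target attainment between the two arms as randomised

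*Protocol*

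**What the plan says.** **The aim.** The Aim section asks whether metformin alone, or metformin with insulin, "is more effective at attaining and maintaining glycaemic targets compared to insulin monotherapy". The Abstract sets the same target-based aim but says that the treatment "is equally effective at attaining and maintaining glycaemic targets compared to insulin monotherapy". The two directions conflict and must be reconciled. The present point holds under either.

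**The targets.** Metformin is increased "to meet glycaemic targets of FBS < 5.1 mmol/L, 1HPG < 10.0mmol/L and 2HPG < 8.5 mmol/L". For the comparator, "The total dose of insulin will be titrated for each patient to achieve the above glycemic targets".

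**The outcomes.** Expected Outcome states: "The primary outcome is the difference in the 2HPG level between the metformin and insulin group". It continues: "Secondary outcomes to be measured include glycaemic profile (measured by FBG, 1HPG, and HB1AC), fetal birth weight, maternal weight gain and caesarean section rate", and adds NICU admissions. The Abstract explains the choice of primary: "The 2-hour post prandial glucose (2HPG) level is the measure selected to estimate the effectiveness of glycaemic control".

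**The one target-based category.** Women whose targets are not met at the maximum metformin dose are given insulin, and the Metformin Group section then says: "Subjects that receive supplemental insulin will be excluded from the metformin group and analyzed for the purpose of this study as treatment failures". The Insulin group section has no matching category. Women who miss their targets there are admitted and re-titrated, and they stay in their group.

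**The concern.** The aim is about meeting numeric thresholds and continuing to meet them. The listed outcomes are levels and clinical events. A reader of the results would learn how far mean 2HPG differs. No planned outcome would say whether more women reached all three targets in one arm, or stayed there.

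The removal of supplemented women makes this worse. The metformin group that enters the comparison consists of women who did not need added insulin, which largely means women who were at target on metformin alone. Insulin women with the same difficulty are kept. The compared groups therefore differ by selection on the very event that the aim asks about, and the metformin-plus-insulin strategy is not tested as allocated.

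If no attainment outcome is fixed in advance, a statement about targets in the report would rest either on a mean of one of the three measures or on a definition chosen after the data are seen.

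**Working it through.** **1. Aim set against outcomes**

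| Element of the aim | Nearest item in the protocol | Two-arm outcome? |
|---|---|---|
| Reaching all three targets | Mean 2HPG (primary); FBG and 1HPG levels (secondary) | Levels only; no count of women at target |
| Keeping them | Repeated-measures ANOVA of glycaemic trends (Statistical Analysis) | Levels over time; no count of visits at target |
| Failure to reach targets | Treatment failure (Metformin Group) | Metformin arm only |
| Metformin with insulin as a strategy | Supplemental insulin requirement and glucose profile (Specific Objectives) | Described within metformin; those women leave the metformin group |

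The z-test for proportions in Statistical Analysis is tied to no attainment outcome.

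**2. Are the data there?** Data Collection plans 2-weekly glucose checks and names FBG, 1HPG and 2HPG as the profile. These are the three measures that carry targets. Attainment can be derived in both arms without new samples.

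**3. What the sample size implies.** Inputs from Sample Size Determination: difference 4 mg/dl (0.22 mmol/l) in mean 2HPG at 34 weeks, power 80%, α = 0.05, 47 per group, 52 recruited. The 52 agrees with 47 × 1.1 = 51.7. No SD is given, so the 47 cannot be reproduced. It can only be solved backwards:

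SD = 4 × √(47/2) / (z_α + z_power)

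- One-sided, as in Statistical Analysis: 4 × 4.848 / (1.645 + 0.842) = 7.8 mg/dl (0.43 mmol/l).
- Two-sided: 4 × 4.848 / (1.960 + 0.842) = 6.9 mg/dl (0.38 mmol/l).

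**4. Is the design powered for attainment?** Take the most favourable case for the 2HPG target: normal data, the implied common SD, and the cut-off midway between the two means. The design difference then moves the proportion at target by 2Φ(2/SD) − 1.

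- SD 7.8: 2Φ(0.256) − 1 = 20 points (40% v 60%). Power with 47 per group is about 63% one-sided.
- SD 6.9: 2Φ(0.289) − 1 = 23 points (39% v 61%). Power is about 60% two-sided.

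Both fall short of 80%. With assumed rates of 60% v 75%, power is 46% one-sided or 34% two-sided, and 80% power would need 120 or 152 per group.

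**5. Precision of an attainment difference.** The protocol gives no attainment rates, so p is assumed equal in both arms:

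half-width = 1.96 × √(2p(1 − p)/n)

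| Assumed p | n = 47 | n = 52 |
|---|---|---|
| 70% | 1.96 × √(0.42/47) = 18.5 points | 1.96 × √(0.42/52) = 17.6 points |
| 85% | 1.96 × √(0.255/47) = 14.4 points | 1.96 × √(0.255/52) = 13.7 points |

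The widest case is p = 50% with n = 47: 1.96 × √(0.5/47) = 20.2 points. Precision for the visit-based outcome cannot be computed, because the protocol has nothing on variation between women.

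**The case against.** The strongest reply is that the protocol has already turned its aim into something measurable. The Abstract names the 2HPG level as the measure of control, Specific Objectives compare glucose profiles, Expected Outcome gives a rationale for 2HPG, and the trend analysis bears on maintenance. A continuous level is also statistically more efficient than a proportion. This stands, and it is why 2HPG can remain primary. It does not supply a statement about all three targets, and it does not bring the combination back into the comparison.

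A second reply is that visit windows and responder definitions usually sit in an SAP, which is not shown here. That is fair for the detailed derivation. The aim, the outcome list and the removal of supplemented women are protocol text, and they do not fit together.

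A reader might infer three stronger claims, and the documents support none of them:

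- *That the trial is unable to answer its question.* The 2-weekly values in both arms allow attainment to be derived. What is missing is a defined outcome.
- *That equal mean 2HPG could hide a large gap in attainment.* With normal data this needs a clearly different spread in the two arms, and nothing in the protocol suggests one. With a common SD, equal means give equal attainment of the 2HPG target.
- *That titration to shared targets makes mean 2HPG uninformative.* Shared titration draws attainment rates together as well, so it is no argument for one measure over the other.

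**Conclusion.** The mismatch is real and should be corrected, but it does not invalidate the design. No listed outcome measures attainment or maintenance of targets in both arms. The single target-based category is one-sided and removes women from the metformin group, so the planned comparison addresses neither the target-based aim nor the combination named in it.

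The size of the resulting bias cannot be stated, because the protocol gives no expected rate of supplemental insulin. The size of what can be learned about attainment can be bounded: with 47 per group the 95% CI for a difference extends about 14 to 20 points either side for assumed attainment between 85% and 50%. Added attainment outcomes are therefore supportive and cannot carry a confirmatory claim. These figures assume complete data in 47 women per group and equal rates in the two arms. The power figures also rest on normal data and on an SD inferred from the sample size.

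**What to change.** Keep 2HPG as the primary outcome. Add to Expected Outcome two secondary outcomes, both derived from the planned 2-weekly values:

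1. The proportion of women meeting all three targets of the Metformin Group section at 34 weeks, the time point used in the power calculation.
2. For each woman, the proportion of scheduled 2-weekly visits at which all three targets are met, counted from one fixed time after randomisation that is the same in both arms. A start defined by the end of titration would not work, because the protocol gives a titration period for metformin (two weeks) and none for insulin.

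For both outcomes, analyse every randomised woman in her allocated arm, including metformin women given supplemental insulin. Report the between-arm difference with a 95% CI. Treatment failure can still be described within the metformin arm. The sentence that excludes these women from the metformin group must be reconciled with the aim.

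State that the two outcomes are supportive and not powered, and give the expected half-widths. Limit any conclusion about reaching and keeping targets to what the intervals support. Otherwise, word the conclusion in terms of mean 2HPG.

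Rewording the aim to mean 2HPG would also remove the mismatch in wording, but by itself it would leave the combination untested as allocated.

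The cost is a few sentences and one table, with no new samples or visits. The price is wide intervals, which must be reported as such.
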